#### Intervention Arm

A total of 6 young, Black, sexual minority men's social networks, each including 5 young, Black, sexual minority men (including index participants) and 1 Black female facilitator, will participate in the intervention arm. Before the trainings, the Black female facilitators completed a baseline survey electronically, which measured sociodemographics, HIV knowledge, PrEP knowledge, HIV-related stigma [53], homophobia [54], and PrEP stigma. Black female facilitators have completed their training on app usage. In addition, Black females also completed an (web-based or face-to-face) intensive training covering (1 day) cultural competence and humility when working with sexual and gender minority populations; experiences of stigma among young, Black, sexual minority men in the South; LGBTQ-focused sexual health topics; and basic information about HIV treatment and prevention, including the use of PrEP and steps required to engage in PrEP care.

All young, Black, sexual minority men in the intervention arm will also receive a training (web-based or face-to-face), including a tour of the downloadable US NoW app, a brief demonstration of how to join and participate in the web-based discussion, and practice on posting content publicly and privately. Once trained, young, Black, sexual minority men will complete HIV testing using OraQuick rapid HIV test (remote participants will be asked to text a picture of the test result via a secure server) and an electronic baseline survey prior to study commencement capturing information on sociodemographics, stigma related to race or ethnicity and sexual practices or orientation [55,56], HIV, poverty, PrEP use [57], PrEP knowledge [57], sexual history and practices [58], alcohol [59] and substance abuse [60], and depression [61] and anxiety [62], using appropriate validated measures. In the event an individual tests positive on an HIV test, they will be referred to the linkage team at the study site’s university-affiliated clinic for counseling, access to confirmatory testing, and linkage to care, if necessary.

Following enrollment of young, Black, sexual minority men and Black women facilitators, 4 predesignated 60-minute discussions with the network and the Black woman facilitator will commence. Activities of Black female facilitators will include leading discussions and answering any questions or comments posted by young, Black, sexual minority men. Young, Black, sexual minority men participants will be instructed how to use the app throughout the 4-week period. The importance of attendance at the discussions will be emphasized and incentivized through app badges given by other members within the network and by Black female facilitators. Additionally, a reminder, through phone texts, will be sent to young, Black, sexual minority men participants about discussion times.

The data collection began in August 2024 and is expected to be completed in December 2025. Once the intervention ends, young, Black, sexual minority men participants will receive follow-up surveys electronically at *T*_1_ (1-month postintervention) and *T*_3_ (3-month postintervention), capturing the primary and secondary outcomes (explained in detail later). Young, Black, sexual minority men will also be asked to perform a rapid HIV OraQuick test at *T*_3_, remotely. Similarly, Black female facilitators will also complete a follow-up electronic survey at *T*_1,_ which will measure feasibility and acceptability, as well as any changes in stigma and PrEP knowledge or attitudes from baseline. In addition to surveys, Black female facilitators will also participate in web-based qualitative interviews at *T*_3_, which will evaluate PrEP knowledge, intersectional stigma, and change in attitudes following the intervention and gain descriptive information about the process (ie, feasibility and acceptability) of PrEP US NoW facilitation. Additionally, experiences and comfort around delivering the intervention will also be assessed.

#### Control Arm

The control arm will be similar to the intervention arm in terms of HIV testing, baseline and follow-up surveys, and incentives. However, there will be no Black female facilitators, and instead of the modified intervention HMP app, these participants will use a control version of the HMP app without any discussions or scheduled check-ins with study staff. These participants will, however, be provided with the opportunity to contact the study team in case of technical difficulties or any other issues.

#### Survey Measures

##### Independent Variables

Using validated measures, the following will be assessed: sociodemographics (age, income, employment, education, insurance, and housing); stigma related to race or ethnicity, sexual practices or orientation, HIV, poverty, and PrEP; PrEP knowledge; sexual history and practices; alcohol and substance abuse; and depression and anxiety.

##### Primary Outcomes

Four primary outcomes—feasibility, acceptability, social capital, and homophobia—will be measured. *Feasibility* and *acceptability* will be measured using responses from *T*_3_ surveys. Validated scales will include the Acceptability of Intervention Measure, Intervention Appropriateness Measure, and Feasibility of Intervention Measure [63]. These scales include straightforward questions such as “[PrEP US NoW] is appealing to me,” to which participants respond on a 5-point Likert scale. Feasibility will also be measured by monitoring in-app usage characterized by the completion of 15-minute discussions, the number of posts, and the total time spent in virtual discussions. Moreover, intervention fidelity will be monitored by documenting the completion of 15-minute discussions and the response rate for questions posted, and by reviewing the accuracy of information shared. *Social capital* will be measured using a modified version of Chen’s Personal Social Capital, the Modified Social Capital Scale [64], adapted for young, Black, sexual minority men use. This scale measures bonding (resources accessed within similar sociodemographic social groups) and bridging (resources derived from cross-identity connections) social capital with sources and types of support (eg, emotional, instrumental, and informational). *Homophobia* will be measured using the Internalized Homophobia Scale [65].

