**Methods:**

First, qualitative information on core health-promoting elements of social capital bonds was captured among young, Black, sexual minority men and Black women in extant social support networks. This information was then applied to adapt an existing, evidence-based mobile health app to create the PrEP US NoW pilot through an unblinded randomized controlled trial. Six social network groups (5 young, Black, sexual minority men + 1 Black woman) will participate in the intervention arm. These will be recruited through a network-based approach and will undergo tailored training (mobile-based and face-to-face) for app usage. At baseline, men will undergo HIV testing and both men and women will complete a sociodemographic survey. The groups in the intervention arm will engage in four 60-minute discussions led by Black women through the modified mobile health app. After the intervention, young, Black, sexual minority men will complete surveys electronically at 1 and 3 months (accompanied by HIV testing) on additional factors such as experiences of discrimination and PrEP stigma. The Black women will complete an electronic survey at 1 month, measuring feasibility and acceptability, and will participate in web-based qualitative interviews at 3 months to gain more knowledge on the PrEP US NoW facilitation process. Participants in the control arm will not engage in Black women–facilitated group discussions and will use a control version of the app. The baseline and follow-up surveys and HIV testing will be documented similarly to the intervention arm.

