The current participant forum in the HMP app was expanded to add a space where the intervention content will be delivered in real time through semistructured discussions led by Black female facilitators with the young, Black, sexual minority men network. Only Black women who possess the qualities identified in the qualitative findings associated with trust and nonstigmatizing support will lead the discussion topics. Black female facilitators and young, Black, sexual minority men network members will have the option of using an avatar to maintain confidentiality. At this time, the intervention mapping process with our CAB has led to the app name being changed to “US NoW.”

Each week, discussions ranging from 30 to 60 minutes will be conducted at a mutually agreed-upon time. Prior to each session, topic-specific scholarly articles suitable for the lay audience and activities will be provided in the HMP app that map the conceptual framework (see Figure 3). Young, Black, sexual minority men's social networks will be asked to view content and engage in discussions during these sessions. The young, Black, sexual minority men participants will be able to communicate and post privately as well as publicly with each other. If Black female leads are contacted ad hoc by a group member (between discussions or 1 week following the last discussion), they will be expected to reciprocate communication or request information within a 24-hour timeframe.

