**Figure 3 figure3:**
[figure not shown]
Community advisory board–informed topics, content, and structure for the intervention. Forum topics track the adapted sIMB conceptual framework. PrEP: pre-exposure prophylaxis; sIMB: situated Information, Motivation, and Behavioral skills; STI: sexually transmitted infection.

Beta testing of the app and intervention was carried out with the CAB to get a sense for how the features will work in the subsequent pilot trial. The CABs were oriented to the app and were asked to use it for a month. During the beta testing, 4 semistructured discussions were convened that mimicked how anticipated sessions will occur during the actual trial. The CAB members reconvened with the study team to provide feedback on their experiences, which was used to make the necessary final changes to the intervention prior to the randomized controlled trial.

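### Feasibility and fidelity count completed 15-minute discussions, but every planned discussion lasts 60 minutes, or 30 to 60

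*Protocol article*

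**What the plan says.** The Primary Outcomes section of the protocol article measures feasibility first by validated scales at the 3-month survey and then, in addition, by app usage: "completion of 15-minute discussions, the number of posts, and the total time spent in virtual discussions". It goes on to say that "intervention fidelity will be monitored by documenting the completion of 15-minute discussions and the response rate for questions posted", together with a review of whether the information shared was accurate.

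The discussions themselves are described in three other places:

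- Abstract, Methods: "four 60-minute discussions led by Black women".
- Intervention Arm: "4 predesignated 60-minute discussions with the network and the Black woman facilitator will commence".
- Translation of Qualitative Findings to Design the PrEP US NoW Intervention: weekly "discussions ranging from 30 to 60 minutes will be conducted at a mutually agreed-upon time".

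The Control Arm section says that control participants use their version of the app "without any discussions or scheduled check-ins with study staff".

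**The concern.** The length attached to completion in the outcome section is not the length of anything the trial plans to deliver. From the visible text, a reader of the eventual completion rate could not tell whether a completed discussion means a full 60 minutes, something between 30 and 60, or a stay of 15 minutes.

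This matters because the facilitated discussions are the main thing the control arm lacks, and the authors recognise attendance as a risk. They plan reminders and app badges to encourage it, and the Discussion allows an extension if networks do not attend reliably. Whether men sit through the sessions is therefore a central feasibility question for any larger trial. If the rule stays unclear until the logs are open, it could also be settled with the results in view. For fidelity the risk is similar: a session cut short at 15 minutes could be recorded as delivered.

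**Working it through.** No formula in the plan is at issue, so the check is a comparison of every stated discussion length.

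| Place in the protocol article | Length | Number |
|---|---|---|
| Abstract, Methods | 60 min | 4 |
| Translation of Qualitative Findings | 30 to 60 min | weekly |
| Intervention Arm | 60 min | 4 |
| Primary Outcomes, feasibility | 15 min | not given |
| Primary Outcomes, fidelity | 15 min | not given |

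**Size of the mismatch per session.**
- Against the shortest planned length: 30 − 15 = 15 minutes short; 15/30 = 50%.
- Against the length in the abstract and the Intervention Arm section: 60 − 15 = 45 minutes short; 15/60 = 25%.

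Fifteen minutes therefore lies outside the whole stated range.

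**Could the figure refer to something else?**
1. *The control arm.* No. It has no discussions.
2. *The beta test.* The text gives no support. It says that "4 semistructured discussions were convened that mimicked how anticipated sessions will occur during the actual trial", and states no length.
3. *An attendance minimum or a segment of a session.* This is possible. The caption of Figure 3 says it covers "topics, content, and structure for the intervention", and the figure is not shown. But the outcome section attaches 15 minutes to the discussions themselves and mentions neither a minimum nor a segment.

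**What the ambiguity does to the count.** Take a man who leaves a 60-minute discussion after 20 minutes. Under a 15-minute mark he has completed it; under a full-session rule he has not. The same log gives two answers.

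**Reach.** The label affects 1 of 3 in-app feasibility indicators (the others are posts and total time) and 1 of 3 fidelity items (the others are response rate and accuracy review).

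**The case against.** The strongest reply is that little depends on this count. Feasibility rests first on the validated scales, and app usage is an addition. The Data Analysis section summarises feasibility descriptively. No visible test or progression threshold uses the completion count, and the margins of error in the Sample Size Justification concern advancement and PrEP uptake. Total time in discussions is collected too, so much of the information survives. All of this stands, and it limits the weight of the point.

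A second reply is that a condensed article may leave the scoring of app logs to a fuller document, and that Figure 3 might explain the 15 minutes. The first part is fair as far as a missing definition of completion goes. But the point here is a figure that the article states, twice, and that disagrees with its own design. Figure 3 leaves open what was meant; it does not change what the outcome section says.

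A third reply is that 30 to 60 minutes may describe the actual duration within a 60-minute slot. That reading is reasonable, so the difference between 60 and 30 to 60 is a minor matter of alignment. It does not bring 15 minutes into range.

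A reader might also infer more than the text supports:

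- *That feasibility as a primary outcome is undefined.* It is not. The scales and the other usage measures are unaffected.
- *That the trial will deliver only 15-minute sessions, a fraction of the planned exposure.* No section plans that.
- *That completion must be scored against fixed totals per man or per network.* The article names no scoring unit, and the possible extension of 5 to 6 weeks means that fixed totals might not match what is delivered.

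**Conclusion.** The inconsistency is real and should be corrected. The outcome section counts completion of discussions at a length that is half to a quarter of what is planned, so the count as written does not match the intervention and could treat partial attendance as completion. The consequence is limited to that one descriptive count, in its feasibility and fidelity uses. The size of any distortion in the reported rate cannot be worked out from the article, because it depends on how many men leave between 15 minutes and the end.

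The conclusion rests on the visible text and assumes that the discussions in the outcome section are the facilitated sessions described elsewhere, since no other kind of timed discussion is mentioned. If 15 minutes turns out to be an attendance minimum or a segment, the sentence still needs to say so.

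**What to change.** In both sentences of the Primary Outcomes section, replace the 15-minute label with completion of the four predesignated discussions at their planned length. Use one length consistently in the abstract, the section on translating the qualitative findings and the Intervention Arm section. If 15 minutes was intended as a minimum attendance mark or as a segment of a session, state that explicitly instead. Either way, settle it before the app logs are summarised. No particular denominator needs to be prescribed.

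The cost is two reworded sentences and one aligned figure, with no new data, participants or analyses. If a 15-minute mark had been the working rule, the completion rate under a full-session rule could only be the same or lower.

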##### Secondary Outcomes

The secondary outcomes will include *connectedness to one’s own ethnic community,* measured using an adapted version of the Social Connectedness in the Ethnic Community Scale [66], *condomless anal intercourse in the past 3 months* (ordinal measures), and *PrEP uptake* (yes or no).

##### Sample Size Justification

For this pilot study, the importance of sample size lies in establishing feasibility and the precision of estimated changes, which will inform the design of future studies. Twelve index participants will be recruited, and each index will provide information to recruit 4 others, yielding a total sample size of 60. Six indexes will be randomized to PrEP US NoW and 6 to the control group. The clustering of participants within the index (specifically the PrEP US NoW group) may result in a reduced effective sample size. Assuming no correlation within indices for all participants, a rate of advancement of 50% for PrEP US NoW, the bootstrap 95% CI would have a margin of error of ±12%. On the other hand, assuming a large correlation, 0.9, the margin of error becomes ±25%. With an anticipated 15% PrEP uptake, the 95% CI margin of error is ±9% for no correlation and ±18% for a correlation of 0.9.

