## Results

For informing the PrEP US NoW intervention, 52 individuals (young, Black, sexual minority men: 33; Black women: 19) completed a web-based screening, which lasted between May 2022 and June 2024. Of these, a total of 30 were selected for semistructured interviews (young, Black, sexual minority men: 15; Black women: 15). The interviews were conducted between May 2022 and June 2024. The findings from the interviews indicated that young, Black, sexual minority men value emotional support the most and that Black women provide both emotional and tangible support (manuscript in the process of submission). These findings were then applied in designing the app for the intervention. The intervention is currently in the initial phases of recruitment. The intervention arm will have 6 social network groups, each comprising 5 young, Black, sexual minority men and 1 Black female facilitator. The control arm is expected to have 30 young, Black, sexual minority men participants. The baseline surveys with young, Black, sexual minority men began in August 2024 and are still ongoing. The baseline surveys with Black females were completed between July and August 2024. The young, Black, sexual minority men's follow-up surveys at *T*_1_ and *T*_3_, along with Black women’s surveys at *T*_1_ and qualitative interviews at *T*_3_, are expected to be completed by the end of 2025. The analysis of findings from young, Black, sexual minority men and Black women in the intervention arm and young, Black, sexual minority men in the control arm will be helpful in assessing the effectiveness of the PrEP US NoW intervention in improving PrEP uptake among young, Black, sexual minority men. If the study shows promising findings, a subsequent grant application will be submitted, which will help develop a fully powered randomized controlled trial that can test the efficacy of the intervention at multiple sites across the US South. In case the findings are not as anticipated, the knowledge gained on young, Black, sexual minority men's social networks, social capital, and the role of Black women facilitators will still provide novel insights to inform future HIV prevention research among this highly impacted group.

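### The ±12%/±25% margins of error given for the PrEP US NoW arm fit all 60 men, not that arm's 30; the 15% uptake margins hold only as figures pooled over both arms

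*Protocol article*

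**What the plan says.** All figures below are from the Protocol article.

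- **Total size (Sample Size Justification):** "Twelve index participants will be recruited, and each index will provide information to recruit 4 others, yielding a total sample size of 60".
- **Allocation (same section):** "Six indexes will be randomized to PrEP US NoW and 6 to the control group".
- **Intervention arm (Intervention Arm section):** six networks, "each including 5 young, Black, sexual minority men (including index participants) and 1 Black female facilitator". The men therefore number 6 × 5 = 30.
- **Control arm (Results):** "The control arm is expected to have 30 young, Black, sexual minority men participants".
- **Precision at a 50% rate (Sample Size Justification):** with no within-network correlation, "a rate of advancement of 50% for PrEP US NoW, the bootstrap 95% CI would have a margin of error of ±12" per cent; then "assuming a large correlation, 0.9, the margin of error becomes ±25" per cent.
- **Precision at 15% uptake (same section):** "the 95% CI margin of error is ±9% for no correlation and ±18% for a correlation of 0.9". No arm is named.

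No denominator is given for any of the four margins. The Data Analysis section sets out GEE logistic models whose target is the contrast in odds of PrEP uptake between intervention and control. No margin is given for that contrast.

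**The concern.** The first pair of margins is tied by name to one arm, and that arm is half the sample. At zero correlation no clustering assumption is involved, so 30 men at a 50% rate should give roughly ±18%. The printed value is ±12%.

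This matters because the section says the sample size is there to establish feasibility and to show how precisely changes can be estimated, with later studies in view. If the margins belong to 60 men pooled over both arms, they describe a quantity that is neither the intervention-arm rate nor an intervention effect. A reader would then expect a tighter result than the design can deliver.

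**Working it through.** **Inputs.** Rates p = 0.50 and 0.15, correlations ρ = 0 and 0.9, and the stated margins, all from the Sample Size Justification. Network size m = 5 and 30 men per arm, from the sections cited above.

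**Formula.** Margin = 1.96 × √[p(1 − p) × DE / n], with DE = 1 + (m − 1)ρ. This gives DE = 1 at ρ = 0 and DE = 1 + 4 × 0.9 = 4.6 at ρ = 0.9.

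**Step 1: reproduce the printed figures with n = 60.**

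- p = 0.50, ρ = 0: 1.96 × √(0.25/60) = 12.65%
- p = 0.50, ρ = 0.9: 1.96 × √(0.25 × 4.6/60) = 27.1%
- p = 0.15, ρ = 0: 1.96 × √(0.1275/60) = 9.0%
- p = 0.15, ρ = 0.9: 1.96 × √(0.1275 × 4.6/60) = 19.4%

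These are close to 12, 25, 9 and 18. The text refers to a bootstrap, so I also simulated one: 1,500 data sets with 1,000 resamples each, resampling individuals at ρ = 0 and whole networks at ρ = 0.9. Twelve networks of 5 gave median half-widths of 12.5%, 25.0%, 9.2% and 18.3%. All four printed figures are recovered to about half a point.

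**Step 2: repeat for one arm and for the difference.** The difference uses 1.96 × √[2p(1 − p) × DE / 30] and assumes the same rate in both arms.

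| | 50%, ρ = 0 | 50%, ρ = 0.9 | 15%, ρ = 0 | 15%, ρ = 0.9 |
|---|---|---|---|---|
| Stated | 12 | 25 | 9 | 18 |
| n = 60, formula | 12.65 | 27.1 | 9.0 | 19.4 |
| n = 60, bootstrap median | 12.5 | 25.0 | 9.2 | 18.3 |
| n = 30, formula | 17.9 | 38.4 | 12.8 | 27.4 |
| n = 30, bootstrap median | 16.7 | 33.3 | 11.7 | 25.0 |
| 30 v 30 difference, formula | 25.3 | 54.3 | 18.1 | 38.8 |

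**Step 3: like-for-like ratios.** Within the formula, one arm against 60 men is √2 = 1.41 times, and the difference against 60 men is exactly 2 times. Bootstrap medians for one arm are 1.3 to 1.4 times the stated values (16.7/12 = 1.39; 33.3/25 = 1.33; 11.7/9 = 1.30; 25.0/18 = 1.39).

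**Step 4: try other bases.**

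- Solving the formula for n from the stated margins gives 66.7, 70.7, 60.5 and 69.5, nowhere near 30.
- The recruitment section also mentions 2:1 randomisation, although its own counts are 30 and 30. An arm of 40 gives 15.5, 33.2, 11.1 and 23.7. An arm of 20 gives 21.9, 47.0, 15.7 and 33.6. Neither fits.
- Sixty men with clustering in the intervention arm only gives 21.2 and 15.1 at ρ = 0.9, against 25 and 18.
- The ρ = 0 difference margins (25.3 and 18.1) happen to equal the stated ρ = 0.9 figures. The text attaches those figures to ρ = 0.9, where the difference margins are 54.3 and 38.8.

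**One figure discriminates poorly.** At 15% and ρ = 0.9, the mean rather than median half-width is 16.1% for 12 networks and 17.5% for 6, so on means the stated 18% lies nearer the 30-man arm. Zero-width intervals pull the means down: if networks were all-or-none, six would contain no user at all in 0.85⁶ = 38% of data sets. The other three figures do not fit 30 men on either summary.

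**The case against.** The best defence is that the margins were meant as pooled figures. No denominator is printed, the zero-correlation assumption is worded to cover all participants, and the 15% sentence names no arm. Read that way, ±9% is exactly right for 60 men and ±18% is about right. This stands for the 15% pair. It does not rescue the 50% pair, which is attached to PrEP US NoW by name.

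A second defence is that this is a pilot with no power claim, reported in a condensed article, so a missing between-arm margin is not an error in itself. I accept that. The between-arm figure belongs in the correction only because a pooled margin could be mistaken for it.

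A reader might infer more than the document supports:

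- **That all four margins are wrong as labelled.** Only the 50% pair carries an arm label.
- **That 15% ± 18% asserts an impossible negative limit.** A ± figure in a planning section is ordinarily a half-width, not a claim that the interval is symmetric, and the 15% sentence does not mention the bootstrap.
- **That the trial will use a bootstrap interval with poor coverage in six networks.** The bootstrap appears only in the planning calculation. The planned analysis is GEE logistic regression with empirical standard errors, and no type of bootstrap interval is specified.
- **That the stated precision is out by half.** That sets bootstrap figures against formula figures. Like for like, the shortfall for one arm is about 30 to 41%.

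**Conclusion.** The concern holds and the text is wrong as written, with moderate severity. The ±12%/±25% pair is assigned to a 30-man arm that cannot deliver it; the margins for that arm are about 1.3 to 1.4 times as wide on a like-for-like basis. The ±9%/±18% pair is acceptable only as an estimate pooled over both arms. It is too narrow for either arm, and about half the width that applies to the between-arm difference.

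The conclusion rests on the following:

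- The 60-man basis is inferred from the arithmetic, not stated.
- Networks are of equal size 5.
- The difference margins assume equal rates in the two arms and are on the proportion scale, whereas the planned model reports odds.
- A correlation of 0.9 is the protocol's own extreme case.

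No test, decision rule or enrolment target depends on these margins, so the severity is not higher than moderate.

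**What to change.** Rewrite the precision statement in the Sample Size Justification so that each margin carries its denominator and method.

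- **Per arm (30 men, 6 networks of 5):** at 50%, about ±18% (no correlation) and ±38% (0.9) by the design-effect formula, or about ±17% and ±33% by median bootstrap. At 15%, about ±13% and ±27%, or about ±12% and ±25%. Pick one method and name it.
- **Pooled:** if any 60-man figure is kept, label it as pooled over both arms and do not attach it to PrEP US NoW.
- **Between arms (30 v 30, equal rates assumed, formula):** add about ±25%/±54% at 50% and ±18%/±39% at 15%, since this is the planned contrast.

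The cost is wording only. No participants are added and the analysis does not change, but the stated precision becomes less favourable.

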### Data Analysis

The data will be stored in a secure server housed in the health system at the University of Alabama at Birmingham and will only be viewed on designated encrypted devices by the principal investigator and study team. Descriptive statistics will be calculated to characterize acceptability and feasibility measures. Stratifying young, Black, sexual minority men by age ranges, 18-21 and 22-29 years, all outcomes will be described by independent variables using frequencies (percentages). Generalized estimated equations will be used to perform logistic regression with empirical standard errors using an exchangeable working correlation, based on the reasonable assumption of equal correlation among members within each index. Other structures will be examined. These models will be used to estimate the rate of PrEP uptake to determine the difference in odds of PrEP uptake, controlling for within-index correlation to determine the difference in the odds of uptake between the two groups (intervention and control). Separate models will be fitted directly after the intervention (*T*_1_) and 3 months following the intervention (*T*_3_). For each model, independent predictor variables (sociodemographic factors, variables related to stigma, knowledge, sexual history and practices, alcohol and substance abuse, and depression and anxiety) will be included as covariates. All categorical outcomes (advancement, change in social capital, connectedness, and condomless anal intercourse in the past 3 months) will be treated similarly. Lastly, if there are overlaps in social networks between index cases, we will perform a network analysis to determine closeness, betweenness, and degree to determine if there will be potential for treatment interference.

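### The precision of a 15% PrEP uptake is stated as a symmetric margin; at correlation 0.9 it implies a negative lower limit and an upper limit about 9 to 12 points too low

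*Protocol article*

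**What the plan says.** The Sample Size Justification of the protocol article rests the sample size on feasibility and on the precision of the estimates, which are meant to inform later trials. The design is given as "Twelve index participants will be recruited, and each index will provide information to recruit 4 others", "yielding a total sample size of 60".

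Two rates are then given a margin:
- For "a rate of advancement of 50% for PrEP US NoW" with no within-index correlation, "the bootstrap 95% CI would have a margin of error of ±12" per cent; and "assuming a large correlation, 0.9, the margin of error becomes ±25" per cent.
- For uptake: "With an anticipated 15% PrEP uptake, the 95% CI margin of error is ±9% for no correlation and ±18% for a correlation of 0.9".

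The word bootstrap stands in the sentence on the 50% rate. The uptake sentence says only that the interval is a 95% CI.

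Under Data Analysis, "Generalized estimated equations will be used to perform logistic regression with empirical standard errors using an exchangeable working correlation". Of these models the article says: "These models will be used to estimate the rate of PrEP uptake", and then the difference in odds between the arms. It does not say how a confidence interval for the rate itself will be formed.

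**The concern.** A margin of plus or minus 18 points is a fair summary for a rate near 50%, where the sampling distribution is roughly symmetric. At 15%, with an effective sample of about 13 men, it is not. Part of the lower arm falls below zero and carries no information, while the upper arm is too short.

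This matters because precision is the stated reason for the sample size. Someone planning the follow-on trial would read the sentence as saying that, even with strong clustering, an observed 15% leaves uptake above 33% implausible. The same inputs leave rates up to the low or middle forties plausible. If the rate were reported with the kind of interval the section names, that interval would also miss the true rate more often than its label says, and mostly in the same direction.

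**Working it through.** **Inputs, all from the Sample Size Justification:** 60 men, 12 networks of 5 (the index man plus 4), uptake p = 0.15, within-index correlation 0 or 0.9, two-sided 95%. Assumed here: equal networks, no dropout, no covariates.

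**Step 1. Reproduce the stated margins.** Effective n = 60 / (1 + 4 × correlation), that is 60 at correlation 0 and 60/4.6 = 13.04 at 0.9. The Wald half-width is 1.96 × √(p(1−p)/effective n). A bootstrap over 12 networks shrinks it by √(11/12) = 0.957.

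| Rate | Correlation | Wald | × 0.957 | Stated |
|---|---|---|---|---|
| 50% | 0 | 12.6% | 12.1% | 12% |
| 50% | 0.9 | 27.1% | 26.0% | 25% |
| 15% | 0 | 9.0% | 8.7% | 9% |
| 15% | 0.9 | 19.4% | 18.5% | 18% |

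Simulated median bootstrap half-widths (beta-binomial networks of 5) were 11.7%, 25.0%, 8.3% and 18.3% in the same order. The stated figures are therefore rounded bootstrap half-widths for all 60 men together. With 30 men the Wald margins for uptake would be 12.8% and 27.4%, which do not match.

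**Step 2. What the margins imply.** Correlation 0: 15 ± 9 = 6% to 24%. Correlation 0.9: 15 ± 18 = −3% to 33%.

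**Step 3. Range-respecting intervals at the same inputs.**
- Logit scale, 0.9: SE of the rate = √(0.1275/13.04) = 0.0989; on the logit scale 0.0989/0.1275 = 0.776; logit(0.15) = −1.735; −1.735 ± 1.52 back-transforms to 3.7% to 44.7%.
- Wilson, effective n 13.04: centre (0.15 + 3.84/26.09)/(1 + 3.84/13.04) = 0.230, half-width 0.188, so 4.2% to 41.8%.
- Clopper-Pearson, effective n 13.04: upper limit 44.9%.
- Correlation 0: logit 8.0% to 26.4%; Wilson 8.1% to 26.1%.

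The gap in the upper limit at 0.9 is 41.8 − 33 = 8.8 points (Wilson) to 44.7 − 33 = 11.7 points (logit). At correlation 0 it is 26.1 − 24 = 2.1 to 26.4 − 24 = 2.4 points.

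**Step 4. Coverage of the bootstrap interval.** Simulation at a true rate of 15%, with 4,000 trials and 1,000 network-level resamples each:
- With 12 networks, the percentile bootstrap 95% interval covers about 92% at correlation 0, 88% to 91% at 0.3, and 82% to 85% at 0.9, over repeated runs.
- At 0.9, about 14% of intervals lie wholly below the true rate and about 1% wholly above.
- With one arm's 6 networks, coverage is about 81% to 84% at correlation 0 and about 58% to 63% at 0.9.
- Wilson on the estimated effective n, using the number of networks when no man or every man reports uptake, covers about 92%, 91% and 94% with 12 networks at correlations 0, 0.3 and 0.9. At correlation 0 it is no better than the bootstrap; the gain comes as correlation rises.
- At 0.9, 8% to 10% of trials with 12 networks have no uptake at all. A logit interval does not exist there, and counted over all trials it covers only 84% to 85%.

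**The case against.** The strongest reply is that nothing here is miscalculated. The margins reproduce, and the article prints a planning half-width, not the range −3% to 33%. That stands: the range is implied, not printed. A percentile bootstrap cannot go below zero; in simulated trials with observed uptake near 15% at correlation 0.9 it runs on average from about 0% to 39%. So a half-width near 18 points is compatible with a higher upper limit than 33%. This also shows why the half-width alone misleads: a reader who is given only a margin has nowhere to place it but around 15%.

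Three stronger readings are tempting, and the documents do not support them.
- A reader might infer that the margin contradicts the logistic GEE under Data Analysis. It does not. That section names no interval for the rate, and a delta-method interval from a logistic GEE is symmetric.
- A reader might infer that the stated margin itself lacks 95% coverage. Taken as a fixed distance, 18 points at correlation 0.9 contains the true 15% in about 94% of trials, and 9 points at correlation 0 in about 95.5%. The shortfall belongs to the bootstrap interval computed from each trial's data.
- A reader might infer a 12-point error throughout. It applies only at correlation 0.9, which the article itself calls large, and is 9 points by Wilson.

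It is also fair that uptake is a secondary outcome of a pilot with no power claim, and that bootstrap is attached to the 50% rate. Its use for uptake is an inference, though the numerical match supports it.

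**Conclusion.** The point holds in a limited form. The half-widths are right for 60 men in 12 networks, but a symmetric margin is the wrong way to state precision for a 15% rate with few networks. At correlation 0.9 it implies an impossible lower limit and understates the upper limit by about 9 points (Wilson) to 12 points (logit); at correlation 0 the difference is about 2 points. The bootstrap interval, if used for uptake, under-covers with 12 networks, modestly at correlation 0 and clearly at 0.9. There is no contradiction between the two sections.

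The size rests on equal networks of 5, no dropout, and all 60 men counted as one group. The article labels the 50% rate as that of the intervention arm, which has 30 men in 6 networks. If the statement is meant for one arm, the limits are wider still: at 0.9 the effective n is 30/4.6 = 6.52 and the logit interval for uptake is 2.0% to 60.2%.

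**What to change.** In the Sample Size Justification, replace the symmetric margins for the 15% rate with lower and upper limits from a range-respecting interval on the effective sample size n/(1 + 4 × correlation). With Wilson and 60 men: about 8% to 26% at correlation 0 and about 4% to 42% at 0.9. Say whether the statement refers to both arms together or to one arm, and recompute for that number. By the same Wilson formula, 30 men give about 6% to 32% (effective n 30) and 3% to 53% (effective n 6.52).

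Under Data Analysis, add that the unadjusted uptake rate will be reported with the same kind of interval, on the estimated effective sample size, using the number of networks as effective n when no man or every man reports uptake. Leave the GEE comparison of the arms as it is.

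The cost is wording and a short recalculation, with no change to enrolment or data collection. The downside is that the stated precision looks less favourable and the reported interval is wider.
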